## Abstract

**Background:**

The success rate of implant-supported prostheses for edentulous patients is relatively high. However, the incidence of biological complications, especially peri-implant mucositis and peri-implantitis, increases yearly after the placement of prostheses. The accumulation of pathogenic bacteria adjacent to a prosthesis is the main cause of biological complications. Titanium, one of the classical materials for implant-supported prostheses, performs well in terms of biocompatibility and ease of maintenance, but is still susceptible to biofilm formation. Zirconia, which has emerged as an appealing substitute, not only has comparable properties, but presents different surface properties that influence the adherence of oral bacteria. However, evidence of a direct effect on oral flora is limited. Therefore, the aim of the present study was to assess the effects of material properties on biofilm formation and composition.

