##### Processing of microbiological samples

Bacterial identification and classification will be determined by sequencing of the V1 and V3 regions of the 16S rRNA gene and amplification by polymerase chain reaction (PCR), as well as library preparations, library quality inspections, and quantifications of DNA samples of the oral flora. The identified TAG sequences will be used for sample differentiation. Qualified libraries will be sequenced with the Hiseq 2500 high-throughput sequencing platform (Illumina, Inc., San Diego, CA, USA). Paired-end reads obtained by Hiseq/Miseq sequencing will be spliced into one sequence and the target sequence subjected to quality control filtering. The filtered sequence will be compared with a reference database, and the chimeric sequence will be removed to obtain the final optimized sequence. Operational taxonomic unit (OTU) cluster analysis and species classification annotations are based on optimized sequences, diversity index analysis is based on OTU clustering results, and species structure and difference analyses are based on taxonomic information. Beta diversity analysis, principal co-ordinate analysis (PCoA), and linear discriminant analysis (LDA) effect size analysis will be used to compare differences in microbial diversity and in significant microbial species between the two treatment groups.

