### Randomization, allocation, and blinding

The subjects will be randomly allocated to one of two groups according to the prosthetic materials: titanium framework with acrylic resin veneering (group 1) or zirconia framework with/without ceramic veneering (group 2). The allocation of patients will be randomized using computer-generated permuted block randomization with an allocation ratio of 1:1. Randomization will be performed by sealed envelopes that will be opened after final impressions are obtained.

Microbiota analysis will be blinded after assignment to the intervention groups. Each sample will have a number associated with an allocation sequence, as well as information pertaining to the dental position and acquisition time. The technician conducting the PCR analysis will be blinded to the source of the sample. Interim statistical analysis will be performed at 1 and 3 years after implantation of the final prostheses. Final statistical analysis will be conducted at the end of the trial with the analyst blinded to both patient allocation and the interim analysis results.

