#### Microbiological monitoring

The mean counts (× 10^5^) of individual bacterial species and the percentage of the total DNA probe will be calculated initially for each implant, then per subject and averaged across patients between groups. Periodontal pathogens include *P. gingivalis*, *Fusobacterium nucleatum* subspecies, and *P. intermedia*, among others. The proportions for the species will be distributed into the six complexes and an “other” group, as proposed by Socransky et al. [27]. Differences in microbiological parameters between groups will be identified using the Wilcoxon signed-rank test. Adjustments for multiple comparisons [28] will be performed when the bacterial species are evaluated simultaneously. The level of significance will be set at 5%.

Alpha and beta diversity analyses will be performed using Primer7 software and the QIIME2 microbiome bioinformatics platform [29, 30]. Alpha diversity, Shannon’s diversity index of both species number and distribution, Margalef’s index of numbers, and Pielou’s index of evenness of distribution [31–33] will be analyzed, and the significance of the differences between groups will be derived using the unpaired Student’s *t* test. Beta diversity analysis includes visualization of data at multiple taxonomic levels, with unweighted and weighted UniFrac distance metrics in order to generate PCoA plots [34]. Analysis of similarity (ANOSIM) will be performed to determine whether there are significant differences in microbial communities between groups. White’s non-parametric test will be applied to test for differences in the abundance of specific microbiota between the groups, with a false discovery rate cutoff of 0.005 with the use of STAMP [35].

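### ANOSIM, the only between-group beta-diversity test named, cannot tell a shift in community composition from a difference in patient-to-patient spread; pair PERMANOVA with a dispersion test

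*Protocol article*

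**What the plan says.** The protocol article, Statistical analysis, Microbiological monitoring, describes beta diversity in two steps. The first is visualisation, with "unweighted and weighted UniFrac distance metrics in order to generate PCoA plots". The second is the test: "Analysis of similarity (ANOSIM) will be performed to determine whether there are significant differences in microbial communities between groups". Significance for the microbiological comparisons is set at 5%.

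The other between-group microbiota comparisons concern single taxa or within-sample diversity. White's "non-parametric test will be applied to test for differences in the abundance of specific microbiota between the groups". Under Processing of microbiological samples, "linear discriminant analysis (LDA) effect size analysis will be used to compare differences in microbial diversity and in significant microbial species"; LDA effect size picks out discriminating taxa and is not a distance-based test. Alpha-diversity indices are compared with a *t* test. ANOSIM is therefore the only inferential beta-diversity comparison in the document, and no test of dispersion is named.

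The Abstract (Background) puts the purpose this way: "the aim of the present study was to assess the effects of material properties on biofilm formation and composition". The Objectives and the outcome sections speak of diversity, and diversity of submucosal species is listed among the primary outcomes.

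**The concern.** ANOSIM compares the average rank of between-arm distances with the average rank of within-arm distances and obtains its p value by shuffling arm labels. Shuffling makes the samples of both arms fully exchangeable. A small p value therefore says that the two distributions differ somehow. It does not say whether the typical community has moved or whether one arm's patients simply differ more from one another.

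The two findings have different meanings. The first supports a statement that the materials carry different bacteria. The second supports a statement that communities are less uniform on one material. With ANOSIM alone the report could not say which was found, on an outcome that is listed as primary and named in the trial title.

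**Working it through.** The plan gives no figure to reproduce here, so the check asks how often ANOSIM rejects when mean composition is the same in both arms and only spread differs.

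**Inputs from the protocol.** 22 per arm, 1:1 allocation, 5% level, 20% dropout. 22 × 0.8 = 17.6, so about 17–18 per arm at the end. Recruitment expects 36 participants, or 36 / 2 = 18 per arm.

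**Assumed inputs.** SD ratios from 1 to 2; one profile per patient; Euclidean or Bray-Curtis distances in place of UniFrac, because no phylogeny is available. 299 label permutations and 500–600 simulated trials per cell in both tables.

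**Statistic.** R = (mean between-arm rank − mean within-arm rank) / [N(N − 1)/4]. For N = 44 the divisor is 44 × 43 / 4 = 473.

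**Why spread matters.** Take two arms with the same centre, *k* dimensions and SDs s1 and s2. Expected squared distances are 2*k*s1² and 2*k*s2² within arms and *k*(s1² + s2²) between arms. With equal arms the within-arm average is also *k*(s1² + s2²), so squared distances balance. PERMANOVA works on squared distances. ANOSIM works on ranks, which do not in general keep that balance.

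**Normal data, same centre, ANOSIM rejection at SD ratio 1.25 / 1.5 / 2**

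| Dimensions | 22 v 22 | 17 v 17 |
|---|---|---|
| 2 | 9 / 29 / 82% | 8 / 22 / 72% |
| 10 | 24 / 86 / 100% | 20 / 72 / 100% |
| 50 | 69 / 100 / 97% | 53 / 99 / 85% |

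With identical distributions ANOSIM rejected in 3–6%. PERMANOVA on the same equal-arm data stayed at 4–7% throughout.

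**Dirichlet-multinomial counts, 100 taxa, same mean composition, Bray-Curtis.** Variance is proportional to 1/(concentration + 1), so the SD ratios are √(51/36) = 1.19, √(51/26) = 1.40 and √(51/13.5) = 1.94.

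| Concentrations | SD ratio | ANOSIM, 22 / 18 / 17 per arm | PERMANOVA, 22 / 18 / 17 per arm |
|---|---|---|---|
| 50 v 50 | 1.00 | 5 / 4 / 6% | 6 / 3 / 6% |
| 50 v 35 | 1.19 | 22 / 16 / 16% | 10 / 8 / 8% |
| 50 v 25 | 1.40 | 86 / 70 / 68% | 36 / 28 / 24% |
| 50 v 12.5 | 1.94 | 100 / 100 / 100% | 100 / 99 / 98% |

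Further runs with equal mean composition and 18–22 per arm gave ANOSIM rejection of 22–39% at a ratio of about 1.25 and 71–99% at 1.5. PERMANOVA on Bray-Curtis counts gave 10–55% over those ratios. Mean R in the equal-arm cells of both tables stayed small, about 0.01–0.18 where spread differed.

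**Unequal arms (normal data).** With 22 v 14 the within-arm pairs number 231 and 91, so the larger arm supplies 231/322 = 72% of the within-arm average. If the smaller arm is the more variable, ANOSIM rejects in 25–100% (ratios 1.25–2). If the larger arm is, it rejects in 0–0.5%.

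**The proposed pairing.** PERMDISP detected a ratio of 1.25 in 80–96% of runs. Calling a result compositional only when PERMANOVA was significant and PERMDISP was not gave a false composition claim in under 2% of unequal-spread runs. For a true shift with equal spread at 18 per arm, power was 86% for ANOSIM and 87% for PERMANOVA.

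**The case against.** The strongest reply is that ANOSIM does what a randomised comparison needs. Patients are allocated at random, so exchangeability is exactly the hypothesis that the material makes no difference, and the test holds 5% under it. If one material makes communities more variable, that is a real effect of the material. The sentence that names ANOSIM speaks only of differing communities, which a difference in spread satisfies. The article nowhere says that a significant ANOSIM will be reported as a compositional shift. Taxon-level tests sit beside it, and a dispersion check could be in an analysis plan that is not shown.

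Most of this stands, and it rules out several stronger readings that a reader might infer:

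- *Inflated type I error, or a material effect that does not exist.* Not supported. The level is correct for the no-effect null. Only the narrower conclusion about composition is unprotected.
- *The sample-size SDs show unequal spread.* They do not. The 0.4 and 0.1 mm values describe bone loss. The bacterial SDs in the same section are no better guide: *P. intermedia* gives 952,117 / 804,935 = 1.18, and *P. gingivalis* is 0 against 36,770. Single-species counts do not measure community dispersion.
- *Optional veneering makes zirconia more variable.* The Randomization and Interventions sections allow zirconia with or without ceramic veneering, while the Abstract, Objectives and Study design specify veneering. That is an inconsistency to reconcile and not evidence on spread.
- *ANOSIM always over-rejects when spread differs.* It does not; with the larger arm more variable it almost never rejected.
- *Replacing ANOSIM with PERMANOVA solves it.* PERMANOVA also rejects on count data with equal mean composition.

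Two parts of the reply do not dispose of the point. Tests of single taxa do not say what a whole-community rejection means. And the choice of test is fixed in the article, not left to a later plan; only the companion dispersion test might be elsewhere.

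**Conclusion.** The point holds as a cheap improvement, not as an error in the validity of the test. ANOSIM answers whether the arms differ in any way. It cannot answer whether they differ in composition, which is the aim in the Abstract, so a significant ANOSIM should not by itself be reported as a difference in composition.

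The size depends on assumptions that the protocol cannot settle. At an SD ratio near 1.25, simulated rejection with equal centres and 17–22 per arm ran from 8% (two dimensions) to 69% (50 dimensions); at 1.5 it ran from 22% to 100%. Unequal arms can push the test in either direction. The protocol gives no community-dispersion figure and UniFrac was not simulated, so these figures show what can happen and do not estimate what will happen in this trial.

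**What to change.** In Microbiological monitoring, amend the beta-diversity test as follows, before any microbiota results by arm are seen:

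1. Test composition with PERMANOVA on the planned weighted and unweighted UniFrac matrices. Use one profile per patient per visit and permute labels over patients. The section already averages species data from implant to subject, so this fits the plan.
2. Always report a PERMDISP test on the same matrices beside it.
3. State the reading rule. When PERMANOVA is significant and PERMDISP is also significant, report a difference in composition and/or variability. When PERMANOVA is significant and PERMDISP is not, a difference in composition may be reported, noting that non-significance does not prove equal spread.
4. ANOSIM R may stay as a descriptive figure.

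This needs no further patients, samples or sequencing, and in the equal-spread setting checked it lost no power relative to ANOSIM (87% against 86%). The cost is one more test to report and a less clear-cut conclusion when dispersion differs, including in some trials where composition has truly shifted.

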### Dissemination of results

The results of the trial will be published in international peer-reviewed journals. A summary of the study results will also be submitted to ClinicalTrials.gov to allow general access.

### Interim analyses

Interim statistical analysis will be performed at 1 and 3 years after the placement of the final prostheses. The analyst will be blinded to the allocation of the patients and will submit the analysis results to the Data and Safety Monitoring Board (DSMB), which will announce an early close to the trial as long as the dropout implant rate exceeds 20%.

### Withdrawal and missing data processing

The patients will be informed at the beginning of the study of the right to withdraw at any time without providing a reason. Even in the event of a withdrawal, the patient will still receive treatment.

If a participant has taken an antibiotic in the last 3 months before a follow-up visit, submucosa samples will be collected, the results of clinical examinations (surface roughness) will be recorded, and X-ray examinations will be conducted. The data obtained from this follow-up will be discarded. However, we still include this participant in the following visits and do the regular periodontal maintenance. If there was no antibiotic use within 3 months prior to the next follow-ups, the data will be recorded.

Any patients who reported smoking during the follow-up period will be excluded from the study.

The possibility of loss to follow-up was considered and calculated as a part of the sample size estimation.

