## Methods and study design

### Study design and setting

The proposed study is designed as a pragmatic randomized controlled trial with a 5-year follow-up period. A Consolidated Standards of Reporting Trials diagram is presented in Fig. 1. We plan to enroll 44 edentulous patients (mandible) in need of dental implant-based prostheses. The goal of the treatment protocol is to rehabilitate these patients with full-arch fixed implant-supported prostheses with placement of 4–6 titanium implants in the mandible. The patients will be randomly assigned to receive restorative materials of zirconia frameworks with ceramic veneering (Fig. 2) or titanium frameworks with acrylic resin veneering (Fig. 3). Both groups will receive titanium implants with sandblasted, large grid, and acid-etched surfaces. The trial will last for 5 years, and the patients will be followed up at 6-month intervals. During each visit, the patient will undergo a clinical examination, surface roughness test, and submucosa plaque collection, while biological and mechanical complications will be treated. One week before each visit, the patient will receive periodontal maintenance, including ultrasonic debridement using an ultrasonic device with polyetheretherketone-coated tips (AIRFLOW® Prophylaxis Master; EMS Dental, Nyon, Switzerland) combined with erythritol air-polishing (AIR-FLOW® handy 3.0 PERIO; EMS Dental). X-ray assessment will be performed yearly. A treatment timeline is shown in Table 1.

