### Primary and secondary outcome variables

The primary outcomes are the implant survival rate, PLI, peri-implant mucosal conditions, marginal bone resorption, and diversity of peri-implant submucosal bacteria species, while the secondary outcomes are the mechanical complication rate and surface roughness of the two treatment groups.

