### X-ray assessment

Marginal bone loss (MBL): immediately after placement of the final prosthesis, a periapical radiograph of each implant will be obtained as well as every year afterward. For standardization, a paralleling technique will be conducted using an intramural digital system (Digora Toto, Soredex, Tuusula, Finland). Kodak Dental Imaging 6.1 software (Carestream Health, Inc., Rochester, NY, USA) will be used for radiographic analysis. The crestal bone level will be measured as the vertical distance between 2 mm below the implant–abutment interface and the most crestal part of the alveolar bone [23, 24]. MBL will be measured mesially and distally for each implant. In each group, peri-implant MBL will be measured to the nearest millimeter.

A peri-implantitis lesion is defined as having PD of ≥ 5 mm with positive suppuration or BI of ≥ 1 and radiographic evidence of bone loss (> 2 mm) or according to consensus [25]. Peri-implant mucositis is defined as being positive for suppuration or BI of ≥ 1 with no radiographic evidence of bone loss. A healthy implant site is defined as a PD of ≤ 4 mm, BI = 0, and no radiographic evidence of bone loss.

The incidences of peri-implantitis and peri-implant mucositis will be determined at 1, 3, and 5 years after final restoration.

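### The antibiotic rule discards a whole visit, not only the plaque sample, and can selectively remove diseased visits; separately, the smoking rule removes randomised patients

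*Protocol article*

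**What the plan says.** Protocol article, Withdrawal and missing data processing, sets two rules.

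- **Antibiotics.** "If a participant has taken an antibiotic in the last 3 months before a follow-up visit, submucosa samples will be collected", and the clinical results (surface roughness is named) and X-rays are obtained as well. Then: "The data obtained from this follow-up will be discarded". The patient stays in follow-up, and later visits count again if they are free of recent antibiotic use. The rule does not distinguish by indication, and the discard is not limited to the microbiota.
- **Smoking.** "Any patients who reported smoking during the follow-up period will be excluded from the study".

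The same section adds: "The possibility of loss to follow-up was considered and calculated as a part of the sample size estimation".

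Four other statements bear on these rules.

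- Primary and secondary outcome variables names five outcomes as primary: "The primary outcomes are the implant survival rate, PLI, peri-implant mucosal conditions, marginal bone resorption, and diversity of peri-implant submucosal bacteria species".
- X-ray assessment: "The incidences of peri-implantitis and peri-implant mucositis will be determined at 1, 3, and 5 years after final restoration". Table 1 schedules implant survival only at Months 12, 36 and 60.
- Study design and setting: patients are examined and sampled at each visit, "while biological and mechanical complications will be treated". The type of treatment is not given.
- Randomization, allocation, and blinding: "Randomization will be performed by sealed envelopes that will be opened after final impressions are obtained". Every follow-up visit is therefore after randomisation.

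**The concern.** Both rules delete randomised data because of something that happens after randomisation.

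The antibiotic rule has a clear purpose for the plaque sample. Nothing in the article extends that purpose to radiographic bone level, implant survival or mechanical complications, yet those data are collected at the visit and then thrown away. If some of the antibiotics were taken for peri-implant infection, the discarded visits would contain more disease than the retained ones. Peri-implantitis and mucositis would then be under-counted, by more points in the arm with more disease. Because disease rates are read at only three time points, one discarded visit can remove a patient from an entire analysis point, and nothing follows Month 60 to replace it.

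The smoking rule is a separate matter. It takes patients out of the randomised comparison because of a behaviour during follow-up. In a trial of 44, each lost patient or visit also costs precision.

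**Working it through.** **Inputs from the article (Sample size):** 5-year bone loss 0.9 ± 0.4 mm and 0.6 ± 0.1 mm; two-sided α = 0.05; β = 0.10; dropout 20%; 22 per group. The article gives no antibiotic rate and no expected peri-implantitis rate, so all such values below are assumptions.

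**1. The plan's own figure.** SD = √((0.4² + 0.1²)/2) = 0.2915 and the difference is 0.3. Two-sided 90% power needs 20 per group by normal approximation (25 after 20% dropout) or 22 by Welch t (28 after dropout). The stated 22 including dropout is not reproduced. That is a separate issue, and the present point does not depend on it.

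**2. Peri-implantitis rate among retained visits.** Let p be the true rate, and let qD and qH be the proportions of diseased and healthy visits discarded, the same in both arms. The observed rate is

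p(1 − qD) / [p(1 − qD) + (1 − p)(1 − qH)].

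Assume true rates of 20% and 10%, a difference of 10 points.

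- qD = 30%, qH = 5%: 0.14/(0.14 + 0.76) = 15.6%; 0.07/(0.07 + 0.855) = 7.6%; difference 8.0 points.
- qD = 60%, qH = 5%: 0.08/(0.08 + 0.76) = 9.5%; 0.04/(0.04 + 0.855) = 4.5%; difference 5.1 points (from unrounded rates).
- qD = qH = 30% (antibiotic use unrelated to disease): 20% and 10%; difference 10 points, unchanged.
- Equal true rates of 20% in both arms, qD = 60%, qH = 5%: 9.5% in both; difference 0.

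**3. Other scales.** The observed odds are the true odds times (1 − qD)/(1 − qH). That factor cancels between arms when it is the same in both. The true odds ratio is (0.20/0.80)/(0.10/0.90) = 2.25. In the first scenario the observed odds ratio is (0.14/0.76)/(0.07/0.855) = 2.25. The shrinkage therefore concerns the absolute rates and their difference.

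**4. Bone loss under the same mechanism.** Bone loss was taken as normal with the article's means and SDs, with the log odds of a discarded visit rising by 0 to 4 per mm of bone loss (assumed). The true difference is 0.30 mm.

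| Log odds per mm | 10% of visits discarded | 20% of visits discarded |
|---|---|---|
| 0 | 0.30 mm | 0.30 mm |
| 1 | 0.28 mm | 0.27 mm |
| 4 | 0.22 mm | 0.17 mm |

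**5. Precision.** After 20% dropout, 22 × 0.8 = 17.6, about 18 per arm. A further 10% of Month 60 visits lost gives 17.6 × 0.9 = 15.8, about 16 per arm. For Welch t, the noncentrality is 0.3/√(0.17/n) and df = (n − 1) × 0.17²/(0.16² + 0.01²) = 1.1245(n − 1).

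- n = 18: noncentrality 3.09, df 19.1, power 0.834.
- n = 16: noncentrality 2.91, df 16.9, power 0.783.

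**6. Smoking.** No arithmetic applies. The Exclusion criteria already remove smokers at entry, so the rule affects only patients who report smoking after allocation. The article gives no expected number of them.

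**The case against.** The strongest case against the point is that the link between antibiotics and outcome is not in the article. Complications are treated, but no antibiotic is named, and the only maintenance described is mechanical. Treatment is placed at the study visits, 6 months apart. A complication found at a visit is recorded at that visit, and a course given then would normally end more than 3 months before the next one. This stands as a limit. It does not remove the point, because the window covers 3 of every 6 months and an infection between visits can trigger the rule.

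A reader might infer that the exclusions do depend on the outcome and do bias the comparison. The article does not support that: no rate, indication or difference between arms is given, and unrelated antibiotic use leaves the difference intact. A reader might also take an extreme case as the expected effect. Discarding half of diseased visits and no healthy ones gives 0.10/0.90 = 11.1% and 0.05/0.95 = 5.3%, a difference of 5.8 points. But the rule applies to any antibiotic for any reason, so a zero loss of healthy visits is not realistic.

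Three further objections hold in part.

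- **Recovery.** Bone level is measured yearly and implant loss is lasting, so a discard at Month 12 or 36 removes that time point but not the 5-year result. A discard at Month 60 cannot be recovered.
- **Clinical signs.** Recent antibiotics might alter bleeding and suppuration, through which disease is defined. Keeping those visits could then also under-count disease. This calls for a sensitivity analysis. It is no reason to delete bone level or implant status.
- **Smoking.** Nothing ties starting to smoke to outcome or arm, and few patients may be affected. The smoking rule should not be described as outcome-dependent.

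**Conclusion.** The point holds in a limited form. As written, the plan deletes collected primary-outcome data after any recent antibiotic use, with a rationale that reaches only the plaque sample. The rule can bias the absolute difference in peri-implantitis toward zero. Under assumed true rates of 20% and 10%, with 30% to 60% of diseased and 5% of healthy visits discarded alike in both arms, 10 points become 8.0 to 5.1. The odds ratio is unaffected under equal discarding, and a true difference of zero stays zero. If antibiotic use is unrelated to outcome, the cost is precision alone: about 83% to about 78% Welch power for bone loss if a further 10% of Month 60 visits are lost. Neither the actual direction nor the size of any bias can be computed from the article.

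The smoking rule is a departure from analysis as randomised. Its size is unknown, and dependence on outcome or arm is not shown.

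**What to change.** Reword Withdrawal and missing data processing as follows.

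- Keep radiographic, implant-survival and mechanical data from every visit, whatever the antibiotic use.
- Exclude only that visit's microbiota sample from the main microbiota analysis, and add a sensitivity analysis that includes it.
- Keep plaque, bleeding, suppuration and probing data in the main analysis, and add a sensitivity analysis that omits antibiotic-affected visits, since these signs might be altered.
- Record antibiotic use by visit, with its indication, so that the link to outcome can be examined.
- Follow and analyse patients who start smoking as randomised, record smoking by visit, and use their exclusion only as a sensitivity analysis.

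**Cost.** For antibiotics this is mainly a wording change, because the article already has the examinations carried out at these visits. For smokers it means continuing the scheduled follow-up. The downside is small: some added noise from smokers and from clinical signs recorded after antibiotics.
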